**Methods:**

The design is a parallel group randomized controlled trial. Participants are allocated to a 3-week self-help intervention plus care as usual or a 3-week waiting period with only care as usual. There are follow-ups after 6 weeks and 18 weeks. At least 80 participants with COVID-19 pandemic related psychological distress will be recruited. Primary outcome are depressive symptoms. Secondary outcomes include anxiety and chronic stress, suicidal experiences and behavior, health-related quality of life, generalized optimism and pessimism, embitterment, optimistic self-beliefs, emotion regulation skills, loneliness, resilience, and the satisfaction with and usability of the self-help program.

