### Trial design {8}

The study is a parallel group RCT comparing an internet-based self-help intervention combined with care as usual (CAU) to a waiting control condition with only CAU. The study flowchart is displayed in Fig. 1. Participants in the waiting control condition receive access to the intervention 3 weeks after the baseline questionnaire. Eligible participants are randomly allocated to one of the two conditions in a 1:1 allocation ratio.

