### Sample size {14}

To specify the sample size needed for the different analyses, we conducted a power analysis based on a probability level of 0.05 and a power of 0.80 with G*Power [53] for a repeated-measures ANOVA with a within-between-interaction. To test the efficacy of the self-help program compared to the control condition, we expected a small-to-medium between group effect size of *d* = 0.35 and a correlation between the factors of at least *r* = 0.4. The expected effect size is based on the results of meta-analyses on the effectiveness of unguided internet-based self-help programs targeting depressive symptoms [17, 54]. We decided to base the expected effect size on unguided internet-based self-help programs as it is yet to be determined if a guidance on demand approach yields higher effect sizes than unguided self-help [23, 24] . Power analysis indicated a necessary sample size of 80 individuals. In consideration of a possible attrition rate between 5.4 and 45.5% at post-assessment, we aim to recruit between 80 and 120 participants at baseline [17].

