## Statistical methods

### Statistical methods for primary and secondary outcomes {20a}

We will use linear mixed models with time (pre versus post-intervention measures) as a within-group-factor and study condition (immediate access versus control condition) as a between-group-factor to evaluate the efficacy of the internet-based self-help intervention. This primary analysis will be performed using the data from the baseline and the 3-week post assessment. To analyze the stability of the short-term effects of the internet-based self-help intervention, we will conduct within-group analyses using repeated measures ANOVA (pre-intervention, post-intervention and follow-up measures) and paired *t* tests when comparing only two time points.

Moreover, we will exploratory analyze possible predictors, mediators, and moderators for the relationship between the internet-based self-help program and the outcomes. The significance level is set at 5%. Analyses will be conducted using SPSS and R.

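### The recruitment range of 80 to 120 does not cover the plan's own attrition range: 80 allows for no loss, and 120 falls short at 45.5%

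*Protocol article*

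**What the plan says.** The section Sample size {14} of the protocol article reports "a power analysis based on a probability level of 0.05 and a power of 0.80 with G*Power", "for a repeated-measures ANOVA with a within-between-interaction". The inputs are "we expected a small-to-medium between group effect size of" d = 0.35 "and a correlation between the factors of at least" r = 0.4, and the result is 80 individuals. The section then turns to losses: "In consideration of a possible attrition rate between 5.4 and 45.5% at post-assessment, we aim to recruit between 80 and 120 participants at baseline".

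The Methods paragraph of the abstract gives only the floor: "At least 80 participants with COVID-19 pandemic related psychological distress will be recruited".

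Three other places matter. The statistical methods section {20a} plans a linear mixed model and says "This primary analysis will be performed using the data from the baseline and the 3-week post assessment". The missing data section {20c} keeps all randomised participants in the analysis and plans multiple imputation. Trial status gives 99 participants in January 2021, with recruitment expected to run to about April 2021.

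**The concern.** The sentence presents 80 to 120 as the requirement of 80 after allowance for 5.4 to 45.5% attrition. The lower end equals the requirement itself, so nothing has been added even for the smallest loss the plan foresees. The upper end is half as much again, which offsets a loss of one third, not of 45.5%.

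At stake is the power of the primary comparison. It uses only baseline and week 3, so a participant lost at week 3 supplies no primary endpoint value. A reader of the section would conclude that 80% power is protected over the stated attrition range, and it is not.

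**Working it through.** **Inputs.** Two-sided 5% level, power 0.80, d = 0.35, r = 0.4, required N = 80, attrition 5.4 to 45.5% and recruitment 80 to 120 (all from Sample size {14}); two arms at 1:1 (Trial design {8}: "Eligible participants are randomly allocated to one of the two conditions in a 1:1 allocation ratio"); two measurements (section {20a}).

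**Step 1: reproduce the 80.** For the within-between interaction with f = d/2 = 0.175 and m = 2 measurements, the noncentrality is λ = f² × N × m/(1 − r), with 1 and N − 2 degrees of freedom. At N = 80, λ = 0.030625 × 80 × 2/0.6 = 8.17 and power is 0.806. The smallest N reaching 0.80 is 79, or 80 with equal arms. The plan's 80 reproduces on these inputs and is taken as given below.

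**Step 2: inflate, counting participants with a week-3 assessment.** N/(1 − attrition):
- 80/(1 − 0.054) = 84.6, so 85
- 80/(1 − 0.455) = 146.8, so 147

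The highest attrition at which 120 still leaves 80 is 1 − 80/120 = 33.3%. The stated 120 is close to 80 × (1 + 0.455) = 116.4, the common slip of multiplying by one plus the attrition rate. The document does not show its step, so that origin is only an inference.

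**Step 3: inflate under the planned mixed model.** Allocation follows a completed baseline, so participants lost at week 3 still contribute a baseline value. With unit variances and data missing at random, the variance of the interaction estimate is proportional to

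(1 − r²)/n_completers + (1 − r)²/n_randomised = 0.84/n_completers + 0.36/n_randomised,

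against 2(1 − r)/n = 1.2/n for n complete cases. The equivalent number of complete cases is therefore n_e = 1.2/(0.84/n_completers + 0.36/n_randomised). Setting n_e = 80 gives N = 80 × [0.84/(1 − attrition) + 0.36]/1.2:
- at 5.4%: 83.2, so 84
- at 45.5%: 126.8, so 127

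For N = 120, n_e = 80 requires 0.84/n_completers = 1.2/80 − 0.36/120 = 0.012, so n_completers = 70 and attrition = 1 − 70/120 = 41.7%.

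**Step 4: power at the stated sizes**, with the Step 1 formula applied to expected completers and to n_e:

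| Randomised | Attrition | Completers | Power, completers | n_e | Power, mixed model (missing at random) |
|---|---|---|---|---|---|
| 80 | 5.4% | 75.7 | 0.783 | 76.9 | 0.790 |
| 80 | 45.5% | 43.6 | 0.540 | 50.5 | 0.605 |
| 99 | 45.5% | 54.0 | 0.634 | 62.5 | 0.700 |
| 120 | 5.4% | 113.5 | 0.921 | 115.4 | 0.926 |
| 120 | 45.5% | 65.4 | 0.721 | 75.7 | 0.784 |

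Rounding 75.7 completers up to 76 gives 0.785. In the last row, using 118 denominator degrees of freedom in place of n_e − 2 gives 0.788, so 0.78 to 0.79 is a fair statement. The mixed-model column is slightly optimistic, because it treats the regression of week 3 on baseline as known: the gain in information at 45.5% is 75.7/65.4, about 16%, and about 14% in a quick simulation that estimated the slope.

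**The case against.** The strongest reply is that the plan does not analyse completers. It keeps every randomised participant, fits a mixed model and imputes. Much of this stands. Baseline values of participants lost at week 3 do carry information, and under missing at random the upper end is short by about 7 (127 against 120), not by 27 (147 against 120). A reader might infer that 85 to 147 is simply the correct range; the documents do not support that, because it belongs to a completers-only analysis. Nor does the number analysed fall below 80, since all randomised participants are included. What falls is the number with an observed week-3 value, and neither imputation nor the model restores all of that information. If data are not missing at random, the gain is smaller or uncertain.

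It can also be said that 120 is enough over most of the attrition range, and that the lowest figures are already out of date. Both are true. The trial had 99 participants in January 2021, so the case of 80 recruits and 44 completers will not occur. Those 99 cover attrition up to 1 − 80/99 = 19% by completers, or about 25% under missing at random.

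A reader might further infer that a range lets unblinded staff choose when to stop. The documents do not support this: no interim analyses are planned, and an approximate end of recruitment is given. A range is not in itself an error.

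**Conclusion.** The concern holds as a mismatch between figures stated in the same section. The lower end of 80 fails at every attrition rate the plan names, by completers and under the mixed model alike. The upper end of 120 fails only at the top of the range: above 33% by completers, above about 42% under missing at random. At 45.5% the power for 120 is about 0.72 to 0.79, against the planned 0.80, so under the planned analysis the shortfall is modest.

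This rests on the plan's 80, on r = 0.4 and, for the milder figures, on missing at random. Whether d = 0.35 was rightly entered as f = 0.175 for an interaction is a separate question and is not judged here.

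**What to change.** In Sample size {14}, replace the range with one recruitment target within the declared maximum, for example 120. State what that target covers: 80 participants with a week-3 assessment up to 33% attrition, or the information of 80 complete cases up to about 42% if data are missing at random. Add the power at 45.5% attrition, about 0.72 by completers and 0.78 to 0.79 under the mixed model, with the missing-at-random assumption named. Replace the floor of 80 in the abstract with the same target.

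A target of 120 does not fully cover 45.5%; the purpose is that the text says so. The cost is rewording in two places. No recruitment above the declared maximum is needed, and recruitment was still open at 99.

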### Recruitment {15}

Participants are recruited from the general population via the study web page. This study web page is advertised on various websites, internet forums and social media. The study web page includes information about the self-help program and the study. People interested in participating can leave their e-mail address on the study homepage and will then be sent the detailed participant information per e-mail.

## Assignment of interventions: allocation

### Sequence generation {16a}

Eligible participants will be randomly allocated to either the intervention or the waiting control condition with a 1:1 allocation ratio as per a computer generated randomization schedule using randomly permuted block sizes by Randomization.com [55].

### Concealment mechanism {16b}

The allocation schedule was generated by an independent researcher and is unknown to the investigators. Allocation takes place after the baseline assessment has been completed. Since the allocated condition is not known until the interested individual has been recruited into the trial, allocation concealment is ensured.

### Implementation {16c}

All interested individuals who give written informed consent for participation and who fulfill all the inclusion criteria and none of the exclusion criteria will be randomized. Staff members responsible for recruitment and data management will ask the independent researcher to randomize respective individuals. In return, the independent researcher informs the staff members per e-mail about the allocation. Finally, the staff members inform the individual about the assigned condition per e-mail.

## Assignment of interventions: blinding

### Who will be blinded {17a}

The staff members are not blinded to the allocation. However, all assessments are performed online with self-report questionnaires. Since participants either receive direct access to the self-help program or have a waiting period, participants are neither blinded to their allocation.

### Procedure for unblinding if needed {17b}

Not applicable since no blinding is performed.

## Data collection and management

### Plans for assessment and collection of outcomes {18a}

All data is assessed online by means of questionnaires programmed in Qualtrics [26]. In addition, data on the use of the self-help program (e.g., number of logins or processed pages) is collected within the self-help program.

### Plans to promote participant retention and complete follow-up {18b}

The participants are asked by e-mail to complete the online questionnaires. If participants fail to complete a questionnaire, they will be reminded by e-mail to do so: for post measurement, they will be reminded after 5 and 10 days and for follow-up measurements after 7 and 14 days. All participants are asked to complete the online questionnaire at each point of measurement, regardless of protocol adherence or any previously uncompleted online questionnaires.

### Data management {19}

Data quality is ensured through several mechanisms, including referential data rules, valid values, range checks, and consistency checks. The option to choose a value from a list of valid codes and a description of the meaning of the code will be available where applicable. Checks are applied at the time of data entry into a specific field. All data collected is stored on a firewall-encrypted back-upped server of the University of Bern with strictly regulated access only for researchers directly involved in the study.

### Confidentiality {27}

All data concerning participant information will be stored in locked file cabinets only accessible for staff members. All collected data will only be traceable by a code. All files containing names or other personal identifiers, such as the informed consent forms, will be stored separately from data containing this code number.

### Plans for collection, laboratory evaluation, and storage of biological specimens for genetic or molecular analysis in this trial/future use {33}

Not applicable since no biological specimens are used.

## Statistical methods

### Statistical methods for primary and secondary outcomes {20a}

We will use linear mixed models with time (pre versus post-intervention measures) as a within-group-factor and study condition (immediate access versus control condition) as a between-group-factor to evaluate the efficacy of the internet-based self-help intervention. This primary analysis will be performed using the data from the baseline and the 3-week post assessment. To analyze the stability of the short-term effects of the internet-based self-help intervention, we will conduct within-group analyses using repeated measures ANOVA (pre-intervention, post-intervention and follow-up measures) and paired *t* tests when comparing only two time points.

Moreover, we will exploratory analyze possible predictors, mediators, and moderators for the relationship between the internet-based self-help program and the outcomes. The significance level is set at 5%. Analyses will be conducted using SPSS and R.

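### The primary time-by-condition model treats baseline PHQ-9 as an outcome with arm-specific means; it is valid, but adjusting for baseline would be more precise at no cost (30% of the information at r = 0.4, less at higher r)

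*Protocol article*

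**What the plan says.** The section on statistical methods for primary and secondary outcomes {20a} specifies "linear mixed models with time (pre versus post-intervention measures) as a within-group-factor and study condition" as the between-group factor. It limits the data to two occasions: "This primary analysis will be performed using the data from the baseline and the 3-week post assessment". Baseline PHQ-9 therefore enters as one of the two outcome measurements. No baseline covariate is named, and neither is a common baseline mean for the two arms.

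That section does not write out which term carries the treatment effect. The sample size section {14} settles the natural reading, because it powers the trial "for a repeated-measures ANOVA with a within-between-interaction", using "a probability level of 0.05 and a power of 0.80 with G*Power". Its inputs are "we expected a small-to-medium between group effect size of" d = 0.35 "and a correlation between the factors of at least" r = 0.4, and its result is 80 participants.

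On timing, the concealment section {16b} says: "Allocation takes place after the baseline assessment has been completed". Participants are "randomly allocated to one of the two conditions in a 1:1 allocation ratio".

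**The concern.** Randomisation after baseline makes the expected baseline PHQ-9 the same in both arms. A model that still estimates a separate baseline mean per arm, and subtracts the observed baseline difference in full, spends information on a quantity already known to be zero in expectation. When the correlation between the two occasions is moderate, that full subtraction adds more noise than it removes.

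What is at stake is the precision of the primary comparison, and so the power and the width of its confidence interval. The baseline score that would recover this precision is already collected from every participant.

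**Working it through.** **Inputs.** From the sample size section: d = 0.35, r at least 0.4, two-sided 0.05, power 0.80, N = 80, attrition at post-assessment 5.4% to 45.5%. From the trial design section: 1:1 allocation. Assumptions not in the article: equal SD at both occasions (relaxed in step 5) and the values of r above 0.4.

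**1. Reproduce N = 80.** For a within-between interaction with 2 groups and m = 2 occasions, the noncentrality is λ = f²·N·m/(1 − r), with 1 and N − 2 degrees of freedom. Taking f = d/2 = 0.175 and r = 0.4 gives λ = 0.030625 × 80 × 2/0.6 = 8.17 and power 0.806, and 80 is the smallest even N that reaches 0.80. Entering f = 0.0875 gives 310, and f = 0.35 gives 22. So the powered test is the 2 × 2 time-by-condition interaction. The change-score t test reaches the same power of 0.806 at N = 80 for a between-arm difference in change of 0.70 SD, so that is the effect the calculation implies.

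**2. Equivalence to a change-score test.** On one simulated complete dataset (40 per arm), the mixed-model interaction and the t test on change gave the same estimate (−0.5322) and the same standard error (0.2594).

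**3. Variance of the treatment estimate, per arm, in units of SD²/n, at r = 0.4.**

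| Comparison | Formula | Value |
|---|---|---|
| Change score (planned interaction) | 2(1 − r) | 1.20 |
| 3-week score only, baseline ignored | 1 | 1.00 |
| 3-week score adjusted for baseline | 1 − r² | 0.84 |

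The ratio is 0.84/1.20 = 0.70, so 30% of the information is lost. In 20,000 simulated trials with 40 per arm the ratio was 0.706. In general the loss is 1 − (1 − r²)/[2(1 − r)] = (1 − r)/2.

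| r | 0.4 | 0.5 | 0.6 | 0.8 |
|---|---|---|---|---|
| Loss | 30% | 25% | 20% | 10% |

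**4. Dropout.** Suppose participants with only a baseline score stay in the likelihood, and a fraction a has no 3-week score. The free-baseline variance is then (1 − r²)/(1 − a) + (1 − r)², and the common-baseline variance is (1 − r²)/(1 − a). At r = 0.4:
- a = 5.4%: 1.248 against 0.888, loss 28.8%
- a = 45.5%: 1.901 against 1.541, loss 18.9%

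**5. Unequal SDs.** With baseline SD s0 and 3-week SD s1, the loss is (s0 − r·s1)²/(s0² + s1² − 2r·s0·s1). At r = 0.4:
- s1/s0 = 1.2 (assumed): 0.52²/(1 + 1.44 − 0.96) = 0.2704/1.48 = 18%
- s1/s0 = 1.5 (assumed): 0.40²/(1 + 2.25 − 1.20) = 0.16/2.05 = 8%

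The loss is zero when r·s1 = s0, and it exceeds 30% if s1 is below s0.

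**6. Power at 80 completers, r = 0.4, equal SDs (noncentral t).**

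| True difference | Change score | Baseline-adjusted |
|---|---|---|
| 0.70 SD (the scale that reproduces N = 80) | 0.81 | 0.92 |
| 0.35 SD at 3 weeks | 0.29 | 0.39 |

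**The case against.** The strongest reply is that nothing here is contradictory. The interaction is a valid test, the sample size was computed for that same test, and preferring another valid estimator is a matter of taste. The first two parts stand. The third does not follow: the covariate is already collected, allocation comes after it, and the gain costs neither participants nor validity. At r = 0.4 with equal SDs the planned comparison is even less precise than one that ignores baseline (1.20 against 1.00).

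A second reply is that the methods section names two factors without writing the model out, so a fuller analysis plan, not shown, might already constrain the baseline means. That is possible. But the time-by-condition interaction is the usual meaning of such a description, and it is the effect the sample size section powers. A plan that adjusted for baseline would need this text aligned with it.

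A third reply concerns size, and it stands. The 30% figure belongs to r at its stated minimum, complete data and equal SDs. The article plans to analyse everyone randomised, and to require a PHQ-9 score above 4 at entry. The entry cutoff may compress the baseline SD relative to the 3-week SD. Both features can shrink the loss.

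Three stronger readings are tempting and are not supported:
- **That the primary analysis is biased, or distorted by chance baseline imbalance.** Imbalance averages out over randomisations, and its contribution is already inside the 1.20 against 0.84 comparison. It is not a second defect.
- **That adjustment gains for every r below 1.** This needs equal SDs (step 5).
- **That this model leaves the trial far short of its stated power.** The figure of 0.29 depends on taking d = 0.35 as a 0.35 SD difference at 3 weeks, which is a separate question about how the effect size was entered. On the scale that yields N = 80, the planned test meets its target.

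**Conclusion.** The point holds as a loss of efficiency in the stated primary model. It is neither an error of validity nor an internal contradiction. The loss is 30% only at r = 0.4 with complete data and equal SDs, and it declines to 10% at r = 0.8. At r = 0.4 it is about 29% to 19% over the plan's own attrition range when baseline-only participants are retained, and about 18% if the 3-week SD is 1.2 times the baseline SD. Across the cases worked here the saving ranges from modest to substantial. The conclusion rests on reading the two-factor model as a free-baseline time-by-condition interaction, which the sample size section supports but the methods section does not spell out.

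**What to change.** In the section on statistical methods {20a}, define the primary estimate as the between-arm difference in 3-week PHQ-9 adjusted for baseline PHQ-9. Either form below serves:
- ANCOVA of the 3-week score on condition and baseline score; or
- a mixed model on both occasions with time and time-by-condition as fixed effects and no condition main effect, so that both arms share one baseline mean.

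Use the same form for secondary outcomes that have a baseline value. Satisfaction and usability, measured only after the intervention, are unaffected. Both forms fit the intention-to-treat and multiple-imputation plan already described; the imputation model should contain baseline PHQ-9 and condition.

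The cost is one sentence and no new data. It should be fixed and dated before outcome data are analysed. The version at hand reports recruitment still open and no planned interim analysis, so that was feasible when it was written. The planned sample size need not change on this account.

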**Fig. 1 Fig1:**
[figure not shown]
Flowchart of the study design

The aim of the RCT is to show the superiority of the internet-based self-help intervention combined with CAU to only CAU at the 3-week post assessment. Additionally, there will be 2 follow-up measurements after 6, respectively 18 weeks after the baseline questionnaire. Since at the time of the follow-up measurements both groups have used the internet-based self-help intervention, the groups can no longer be compared. However, we use these follow-up measurements to assess the sustainability of potential treatment gains, i.e., to examine whether the short-term effects of the internet-based self-help intervention are maintained within groups. In addition, the follow-up measurements will be used to explore predictors of the sustainability of potential treatment effects.

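### The repeated-measures ANOVA chosen to show that gains last does not separate kept from lost gains, and its time labels do not fit the waiting arm

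*Protocol article*

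**What the plan says.** Trial design {8} explains that both groups will have used the program by the follow-ups, so the groups can no longer be compared. It keeps the 6-week and 18-week assessments "to examine whether the short-term effects of the internet-based self-help intervention are maintained within groups", and also to explore predictors of sustained effects.

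Statistical methods {20a} names the method for the maintenance question: "we will conduct within-group analyses using repeated measures ANOVA (pre-intervention, post-intervention and follow-up measures"), plus paired t tests for comparisons of two time points, at the 5% level. It names no post-to-follow-up contrast, no interval, and no rule for concluding that an effect was maintained.

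Outcomes {12} counts all visits from baseline: t0, the post-measurement t1 at 3 weeks, and follow-ups t2 at 6 weeks and t3 at 18 weeks. Trial design {8} gives the waiting arm access 3 weeks after baseline, which is at t1.

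Methods for non-adherence and missing data {20c} plans intention-to-treat analysis of all randomized participants with multiple imputation, and sensitivity analyses with and without the imputed data.

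**The concern.** Maintenance is a question about change from post to follow-up. An overall time test across pre, post and follow-up asks only whether any of the means differ. The pre-to-post drop can make it significant by itself, so a significant result does not say whether the gain lasted.

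The paired t test can address the right pair of visits. At this sample size, however, a non-significant result leaves substantial loss quite possible.

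The visit labels add a second problem. If t1 is post for both arms, the waiting arm's change from t1 onward is its first response to the program. A test meant to show stability would then pick up efficacy, without a control group.

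At stake is the conclusion on durability, one of the two stated uses of the follow-up waves.

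**Working it through.** **The plan's own figure.** Sample size {14}: "we conducted a power analysis based on a probability level of 0.05 and a power of 0.80 with G*Power" "for a repeated-measures ANOVA with a within-between-interaction", with d = 0.35 and r = 0.4. Using f = d/2 = 0.175, m = 2 time points and N = 80:

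- λ = f²·N·m/(1 − r) = 0.030625 × 80 × 2 / 0.6 = 8.17, on 1 and 78 degrees of freedom. Power is 0.806, so the stated 80 reproduces.
- With three time points the same formula gives 66, and with four it gives 56. The 80 therefore belongs to the two-time-point primary interaction. No figure is given for the stability analysis.

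**Inputs for the maintenance check.** From the protocol: r = 0.4, and 40 or 60 per arm (80 to 120 recruited, 1:1). Assumed, because the protocol gives no within-group effect: pre-to-post gains of 0.35, 0.5 and 0.8 SD, and equal correlation between all visits. There were 4,000 simulated trials per setting, each with one arm observed at t0 to t3 and no missing data.

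**Overall ANOVA time test, proportion significant at 5%, 40 per arm**

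| True course after t1 | 0.35 SD | 0.5 SD | 0.8 SD |
|---|---|---|---|
| Fully kept | 0.52 | 0.84 | 1.00 |
| Half lost at t3 | 0.47 | 0.80 | 1.00 |
| Fully lost at t3 | 0.65 | 0.93 | 1.00 |
| Fully lost at t2 and t3 | 0.51 | 0.84 | 1.00 |

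The rows hardly differ, and complete loss at t3 gives figures at least as high as full maintenance. At 60 per arm and a 0.5 SD gain, the figures are 0.96 (kept) and 0.99 (lost at t3).

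**Paired t test, t1 versus t3, when half the gain is lost**

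| Per arm | 0.35 SD | 0.5 SD | 0.8 SD |
|---|---|---|---|
| 40: significant | 0.17 | 0.30 | 0.60 |
| 40: loss missed | 83% | 70% | 40% |
| 60: significant | 0.24 | 0.41 | 0.79 |
| 60: loss missed | 76% | 59% | 21% |

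**Interval width.** The SD of a paired change is √(2(1 − 0.4)) = 1.095 baseline SDs.

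- 40 per arm: standard error 1.095/√40 = 0.173; 95% half-width 2.02 × 0.173 = 0.35 SD.
- 60 per arm: standard error 1.095/√60 = 0.141; 95% half-width 2.00 × 0.141 = 0.28 SD.

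At 40 per arm the half-width equals the whole between-group effect of 0.35 that the trial expects.

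**Weeks since program access**

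| Visit | Immediate arm | Waiting arm |
|---|---|---|
| t0 (week 0) | 0, pre | −3, waiting |
| t1 (week 3) | 3, post | 0, pre |
| t2 (week 6) | 6, follow-up | 3, post |
| t3 (week 18) | 18, follow-up | 15, follow-up |

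If t1 is nevertheless used as post in the waiting arm, and its gain occurs between t1 and t2 and is fully kept, the t1-versus-t3 paired test is significant in 0.50, 0.80 and 1.00 of trials (gains 0.35, 0.5 and 0.8 SD, 40 per arm). That result reflects first response to the program.

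**The case against.** **The paired t tests can cover the right comparison.** This stands. Post versus follow-up is a two-time-point comparison. At 40 per arm the test detects complete loss of a 0.35, 0.5 or 0.8 SD gain in 51%, 80% and 99.5% of simulated trials. A reader might infer that the plan would report stable effects almost whatever the truth. The document does not support that: it states no rule that non-significance means maintenance. What remains is that partial loss is often missed, and that the contrast and interval that would answer the question are not named.

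**Contrasts and visit mapping are often left to an analysis plan.** This is fair, and such a plan may exist. But the article itself ties a specific test to a specific question, and the overall test does not answer it.

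**Pre- and post-intervention can be read per arm.** This is possible, so a misaligned analysis is a risk and not a proven error. Against that reading, the primary model in {20a} uses the same terms for both conditions and ties them to baseline and week 3. Outcomes {12} also labels week 3 as post without distinguishing the arms.

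**Further inferences that should not be drawn.**

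- That the main stability analysis discards incomplete cases: {20c} plans multiple imputation, so case deletion could affect only the sensitivity analysis without imputed data.
- That selection on the baseline PHQ-9 score gives a usable size for bias in the maintenance result: regression to the mean acts mainly on pre-to-post change, and any figure needs an assumed mean and SD, as well as a correlation stated only as a minimum.
- That the follow-ups serve maintenance alone: exploring predictors is also stated.

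**Conclusion.** The concern holds in limited form. The overall ANOVA test does not distinguish kept from lost gains: at 40 per arm and an assumed 0.5 SD gain, it is significant in 84% of trials with full maintenance and 93% with full loss by week 18. Non-significance of the paired test is weak support for stability, missing a loss of half that gain in about 70% (40 per arm) or 59% (60 per arm) of trials. Under the protocol's common visit labels, the waiting arm's change after week 3 is a first treatment effect.

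The percentages rest on the assumed gains, equal correlations of 0.4 and complete data. The protocol gives the correlation as a minimum, and a higher value helps. At r = 0.6 with 40 per arm, the standard error is √(0.8/40) = 0.141, the same as at r = 0.4 with 60 per arm, so the miss rate would be near 59%. That the overall test does not isolate post-to-follow-up change does not depend on these values.

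This is a secondary, within-group analysis. The randomized comparison at week 3 is untouched.

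**What to change.** Replace the stability sentence in {20a} with the following:

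1. Analyse t0 to t3 with the linear mixed model already planned for the primary analysis, and keep the missing-data plan in {20c}.
2. Index time from program access. Immediate arm: t0 pre, t1 post, t2 and t3 follow-up. Waiting arm: t1 pre, t2 post, t3 follow-up.
3. Report the post-to-follow-up change with a 95% confidence interval as the maintenance estimate: t1 to t2 and t1 to t3 in the immediate arm, t2 to t3 in the waiting arm. Show the arms separately, because the spans differ (3 and 15 weeks versus 12 weeks).
4. State that non-significance will not be read as maintenance, and describe the result as uncontrolled within-group course.

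A margin set at half the observed week-3 effect should not be added. It would depend on the data, and even half the expected effect (0.35/2 = 0.175 SD) would be excluded by the interval in only about 17% (40 per arm) to 23% (60 per arm) of trials with full maintenance.

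The cost is analysis wording only, with no new data and no change to trial conduct. The downside is a more modest maintenance conclusion, because the intervals will be wide at this sample size.
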